#### Intervention

The EASY Minds program will involve teachers adapting mathematics lessons over a 6 week (3 × 60 min sessions per week) period to ensure movement-based learning is applied to the NSW K-10 Mathematics syllabus [28]. The intervention program will involve a 1 day teacher professional learning day, the provision of equipment and resources, teacher-initiated adaptation of mathematics lessons to incorporate movement-based learning and support for teachers during program implementation.

All classroom teachers from the intervention schools will be invited to attend a 6 hour professional learning workshop conducted at the university and delivered by NR, KH and [name]. The content of the professional learning day is outlined in Table 1. The one day workshop includes a rationale for PA integration, presentation of results from the feasibility trial, practical examples of PA integration and a peer supported planning session.

**Table 1 Tab1:** **EASY Minds Professional Development workshop**

Session	Focus	Content
**1**	Theory Introduction and EASY Minds program objectives	* Research on the effects of a school-based program on physical activity and academic performance.
		* Introduction to the EASY Minds program and key measures.
		* Mathematics: Student engagement in mathematics
		* Managing the learning environment
**2**	Practical Movement-based learning. Practical considerations and key teaching principles.	* Introduction to practical activities that promote mathematical concepts
		* Teachers will expand their repertoire of teaching practices by learning about and participating in activities successfully trialed in schools in advance.
		* Links to key elements of Quality Teaching Framework e.g. quality learning environment Engagement, high expectations, social support, self-regulation.
	Key teaching principles of movement-based learning	* Watching and discussion of previously recorded video footage of movement-based learning lessons filmed by and delivered by research team.
**3**	Theory Planning and delivery	* Teachers will plan an EASY Minds enhanced mathematics unit of work and individual activities using their current mathematics unit of work using both previously prepared resources, knowledge acquired and peer support.
		* Teachers will be instructed in how to utilise current resources and how to embed resource kit provided into their teaching.
**4**	Practical	* Teachers will deliver to their peers both an indoor and outdoor movement-based activity from their lesson plan developed in previous session.
		* Feedback and support from peers via observation and discussion.
**5**	Conclusion	* Recap of key principles of movement-based lessons.
		* Introduction to fidelity checking procedures.
		* Explanation of email support by research team.

The workshop is designed to engage, inspire and equip the teachers with the necessary skills to plan and deliver movement-based mathematics lesson. The professional learning day is registered and accredited with the New South Wales Institute of Teachers and attendees will be given professional learning hours towards their teacher accreditation. Attendees will be familiarized with the increasing evidence linking physical activity with academic performance and evidence related to the consequences of student disengagement from mathematics in the middle years of schooling. They will be provided with demonstrations and resources for learning experiences to promote physical activity across the primary school mathematics curriculum. These activities and resources were previously employed in the successful feasibility trial. The professional learning day will promote two types of mathematical lessons. i) Activities that use PA as a platform for the development of procedural fluency of fundamental number operations [28]. For example, students can recall multiplication tables whilst skipping, throwing and catching a ball or running through drill ladders. ii) Lessons that look at mathematics in the world around the school [29]. For example, estimating and measuring distance, finding shapes and identifying properties of them in the natural environment, data collection and representation involving fundamental movement skills of kicking throwing, striking. Example ideas can be found in Table 2.

**Table 2 Tab2:** **E.A.S.Y. Minds: self evaluation checklist**

(***Please circle and provide comments)***		***(1 = Not at all true***to ***5 = Very true)***				
Mathematical concepts	i) Key mathematical concepts were reinforced throughout the movement-based activity	1	2	3	4	5
	ii) Movement aided and promoted learning	1	2	3	4	5
	iii) Students were given feedback to support their mathematical knowledge and understanding	1	2	3	4	5
Activity levels	i) Transitions were managed smoothly	1	2	3	4	5
	ii) Students assisted in the set-up and collection of equipment	1	2	3	4	5
	iii) Equipment used promoted physical activity	1	2	3	4	5
Engagement	i) Students were engaged by the activities taught	1	2	3	4	5
	ii) Students remained on-task throughout the lesson	1	2	3	4	5
	iii) Students enjoyed the movement-based mathematics lesson	1	2	3	4	5

Following the completion of the professional learning day, all schools will receive an EASY Minds equipment pack containing a selection of sporting and mathematical resources identified in the feasibility trial as being relevant for promoting movement-based learning. This includes, but is not limited to, stopwatches, tape measures, large dice, drill ladders, basketballs, skipping ropes, numbered beanbags, target mats and numbered flexi-domes (value $AU800). All participating teachers will receive a CD-ROM with example movement-based activity descriptions developed by the research team at the culmination of the professional learning day to be used as a guide when integrating PA across their existing mathematics program. These activities are aligned with the current NSW mathematics syllabus An important component of the program is a focus on teacher ownership and a tailored approach to meeting individual school requirements regarding each schools own specific unit of work and as such, the content of lesson material needs to be individually planned and prepared. The professional learning sessions will be delivered by academics (NR, KH and [name]) who are experienced researchers in the fields of physical activity promotion, mathematics education and primary school pedagogy and qualified teachers. Teachers will be encouraged to be creative and to develop their own lessons, thereby developing ownership of the program and increasing the likelihood of sustaining the program beyond the intervention period [18].

A key principal of the EASY Minds program is the alignment of the program with the NSW Quality Teaching Framework [24]. The NSW quality teaching framework encourages teachers to develop innovative skills that promote high levels of intellectual quality, establish a quality learning environment and generates significance by making learning meaningful and purposeful [24].

The intervention will run for 6 weeks during the schools’ regular timetabled mathematics sessions and will be delivered by the regular classroom teacher, who will translate their knowledge from the professional development training to create movement based learning activities for mathematics.. Teachers will be encouraged to integrate PA in Mathematics sessions (60 minutes) on at least three occasions per week whilst maintaining the key focus on the desired mathematical outcomes from the current syllabus. The teachers will all receive a weekly email offering tips and strategies from the research team and a fortnightly fidelity check during weeks 1, 3 and 5 of the intervention.

### Outcomes

Evaluation of the EASY Minds program will involve a variety of instruments and surveys to report on physical activity and key academic variables (on task behaviour, mathematical performance and attitude towards mathematics). All assessments will be conducted by trained research assistants and carried out in a sensitive manner. The collection of height and weight data will be measured behind a portable screen by gender matched researchers. All PA and academic measures will be measured at baseline and post-test (6 weeks).

### Physical activity

The primary outcome will be children’s school-based PA levels. Actigraph accelerometers (GT3X, Pensacola, USA) will be used to provide an objective measure of both PA intensity and duration [30]. The Actigraph accelerometer has acceptable reliability and validity in both children and adolescents [31]. Accelerometers will be worn Monday through to Friday, during school hours only. This will vary slightly for each school setting as the schools are likely to have different start and finish times. The classroom teachers will receive training in how to instruct students to wear accelerometers and be responsible for distributing and collecting the accelerometers on a daily basis. Accelerometers will be attached to an adjustable elastic belt and worn on the right hip. Raw data from the accelerometer will be screened and analysed using Meter plus software version 4.7 which allows for time specific analysis to accurately analyse lesson- and school-time PA. Participants’ PA will be included for analysis if they wear the accelerometer for at least five school hours on any given day. Similarly, students will only be included in the analysis if they wear the accelerometer for 50 minutes of the 60 minute mathematic lessons. This time period may vary from school to school as a result of schools individual timetables. The Evenson cut-points will be used to classify activity as sedentary: (0–100 CPM, light (101–2295 CPM), moderate (2296–4011 CPM), vigorous 4012 - ∞ CPM ) or MVPA [32]. MVPA is a variable calculated by summing moderate and vigorous PA. Data will be collected in 15 second epochs and non-wear time will be defined as 20 minutes of consecutive zero’s [33].

### Academic measures

#### On-task behaviour

Children’s on-task behaviour will be observed using a momentary time sampling procedure. This observational tool has been adapted from the Behaviour Observation of Students in Schools [34] and the Applied Behaviour Analysis for Teachers [35]. Six students per class group of either sex will be selected and observed in 15 second intervals on a rotational basis over a 30 minute period in the allocated mathematics time slot. A cross-section of students with varying mathematical ability will be selected by the classroom teacher from those working above, those working at and those working below the class average as determined by exiting teacher assessments. On-task behaviour will include behaviour that could be categorised as being ‘actively engaged’ or ‘passively engaged’. Actively engaged refers to a child being actively engaged in academic responding, e.g. reading, writing, performing a set task. Passively engaged will be categorised as behaviour where the child is listening to the teacher or a fellow student but is not actively participating in a set task. Off-task behaviour includes behaviour that can be described as being either: ‘off-task motor’ where a child moves in a manner not associated with the task, for example walking around the class; ‘off-task verbal’ includes non-work related talking or ‘off-task passive’ where a child is disengaged but passive, including staring into space. Two trained research assistant observers will observe simultaneously. This method of systematic observation has been recommended when seeking to simply describe the classroom behaviour of children [36]. Classroom behaviour will be reported as a percentage of time.

#### Attitude to mathematics

Participants’ attitudes to mathematics will be measured using a 24-item questionnaire containing two separate subscales: i) Confidence e.g. *I get good grades in maths*, and ii) Usefulness e.g. *Maths is a worthwhile necessary subject*
[37]. Each scale consists of 12 items with six items positively worded and six negative. Studies on the psychometric properties of the scale provide evidence for the reliability and validity of the subscales [38].

#### Mathematic achievement

Mathematics achievement will be measured using a Mathematics Progressive Achievement Test (PAT) [39]. For the purpose of this study cohort, PAT version 3 will be used. The PAT Mathematics test has 37 questions and takes 40 minutes to administer. The test will be administered by the classroom teacher under exam conditions as recommended by the Australian Curriculum for Educational Research (ACER). The 37 questions form separate items for individual mathematics sub-strands. These being number (n = 14), Space (n==6), Measurement (n = 6), Data (n = 5) and Number (no calculator) (n = 6). The test will provide evidence of student’s strengths and weaknesses and change over time.

Demographic information (i.e., age, sex, language, country of birth) will be collected at baseline via questionnaire alongside questionnaires of children’s preferred learning styles and intelligence strengths. These will be used to profile the children recruited in the study. Learning styles will be measured using the Barsch Learning Style Reference Form [40] and students’ preferred perceptual modality will be determined. Preferred perceptual modality (learning style) has been defined as the conditions under which individuals concentrate process and internalise information [41]. The Barsch learning style reference form defines three perceptual modalities. These are kinaesthetic (relating to body movement), visual (relating to the eyes) and auditory (relating to the ears). Students’ intelligence strengths will be assessed using a Multiple Intelligences Checklist for Upper Primary and Secondary (MICUPS) [42].

Weight will be measured in light clothing without shoes using a portable digital scale (Seca 770, Wedderburn) to the nearest 0.1 kg and height will be measured to the nearest 0.1 cm using a portable stadiometer (Design No. 1013522, Surgical and Medical Products, Seven Hills, Australia). Height, weight, learning style and intelligence strengths will only be measured at baseline to profile the sample. No measures will be taken at follow up.

### Process evaluation

The overall feasibility of the EASY Minds program will be examined using a number of metrics to form a detailed process evaluation. Measures of recruitment, retention, adherence and satisfaction from teachers and students will be collected. We will also use a semi-structured discussion framework to conduct focus groups with students and one-on-one interviews with teachers. All questionnaires and focus group interviews for both students and teachers will be conducted by members of the research team. Teachers attending the professional learning session will complete a short evaluation questionnaire, which will assess teachers’ perceptions of the skills and ideas gained from the training, their satisfaction with the quality of the teacher training and their confidence to plan and deliver movement-based mathematics lessons across the study period. A 5-point Likert scale will be used with responses ranging from ‘*strongly disagree’* = 1 to ‘*strongly agree’ = 5*.

For example, i) the practical session improved my confidence to teach PA mathematics lessons, ii) the workshop provided me with useful information and skills that may improve my teaching. Additionally, participants will be asked for suggestions to improve the learning workshop or the program principles to assist further in the teaching of movement-based learning.

Throughout the intervention period, teachers will be asked to complete an activity evaluation log after each session and reflect on their lesson and rate their lesson using a 5-point Likert scale. The teachers will all receive a weekly email offering tips and strategies from the research team and a fortnightly fidelity check via observation during weeks 1, 3 and 5 of the intervention. During this observation, a five minute discussion will take place where teacher and researcher will discuss a self-evaluation/ activity log focused on 3 items. These will be 1) mathematical concepts (n = 3), e.g.; the key mathematical concepts reinforced throughout the movement based activity, 2) activity levels (n = 3) e.g. transitions were manage smoothly and 3) engagement (n = 3) e.g. students were engaged by the activities taught. (See Table 3).

**Table 3 Tab3:** **Example activities from professional learning day**

Mathematics content	Movement-based lesson
Using an Empty number line	• Students are encouraged to use a number line drawn in chalk outside and utilise the jump strategy.
	• Present the students with a number problem. E.g. 8000–673.
	• Students should try to complete the number line in the most efficient way.
	• Assign each “jump” a physical activity. Students can create their own movement
	• 1000 = Squat, 100 = jump, 10’s = lunge, 1’s = bottom kicks.
	• In this case the answer would be 7327. Students would perform 7 squats, 3 jumps, 2 lunges and 7 bottom kicks.
	Students can be presented with a series of operations and be encouraged to use an empty number line.
Multiplication and Division	• Students will throw up to 5 bean bags on to a numbered target. They add up the total. They then divide the total by the number thrown. This will give the mean score.
	• Each child throws two bean bags on to the target. They then roll the 20 sided dice and multiply the number rolled by the total score.
	• Children should be encouraged to estimate their answer and record before actually working out.
Recognising Factors, multiples and prime numbers	• Arrange numbered flexi domes throughout the area with the numbers in random order
	• Students run/skip/hop/side gallop etc. to the flexi dome applicable when the scenario is given.
	• What is one factor of 40? Repeat this question but change the number e.g. 75, 16, 84 etc.
	• Show me a factor of 24, and then hop to the pair of the
	• Find multiples of the number 3.
	• Find a prime number.
Three Dimensional Space	• Identify and describe the properties of three dimensional objects, for example number of faces, apex of a pyramid, number of edges etc.
	• Teachers can ask “How many vertices does a cube have?”
	• Students are to answer by skipping the required amount to answer the question. Students can ask each other and work in pairs.
Two Dimensional Space	Netball court or other marked pitch.
	• Working in small groups students are to classify all shapes they can identify on a netball court.
	• Students are to then draw and measure all key parts.
	• Students need to include length, width, radius, diameter, circumference, semi-circle and diagonals.
	• Using appropriate scale students are to draw an accurate scaled diagram

Upon completion of the 6-week program, all students will complete a process evaluation questionnaire. This questionnaire will be administered to determine students’ perceptions of integrating physical activity within the curriculum focusing on values of enjoyment and mathematical outcomes. A 5-point Likert scale will be used with responses ranging from ‘*strongly disagree’* = 1 to ‘*strongly agree’ = 5*. For example, “*I liked being physically active in Math’s****outside****the classroom*”.

#### Student focus groups and teacher interviews

Focus group interviews will be conducted with the students and phone interviews will be carried out with participating teachers. For the focus groups, two groups of six students per class (mixed sex) will be selected based on a range of mathematical abilities determined by the class teachers. Each teacher will be asked to select two children of higher, middle and lower ability for the class cohort. The 10–15 minute focus groups will use semi-structured questions. The focus group will be conducted by a researcher not directly involved in the current project.

The focus groups will be recorded and later transcribed by an independent third party. Specifically, the questions asked in the students’ groups will be designed to explore their perceptions of the EASY Minds outdoor mathematics lessons and associated activities, their mathematics lessons prior to and subsequent to their involvement in the program, as well as the students’ appraisal of how the EASY Minds lessons had influenced their perception of mathematics, and learning related to mathematical concepts The focus group discussion framework was designed to elicit responses to the following questions: How would you describe your math’s classes before the EASY Minds program? Did you enjoy this? Did you enjoy the outdoor EASY Minds math’s lessons? Why? Can you give me an example? Did this make the math’s activities more interesting? What kinds of activities did you enjoy doing in the E.A.S.Y. Minds program? Can you tell me if being active in math’s classes helped you learn? Why/ why not? If so can you give me an example?

Additionally, a one on one phone interview will be conducted with the teachers involved in the intervention group, after program completion. The 15 minute interview will be recorded and transcribed by an independent researcher. The interviews with teachers will be designed to elicit their perceptions of EASY Minds lessons compared to regular mathematics lessons. Teachers will also be asked to identify major challenges to the implementation of EASY Minds lessons, as well as their appraisal of learning outcomes and students’ enjoyment of the lessons, with particular emphasis on the role of physical activity in student engagement.

The following types of questions will be asked: Did you enjoy teaching an active mathematics session as opposed to a classroom based lesson? What were the major challenges to you as a teacher of active mathematics sessions? Do you think your students enjoyed the lessons/why/ why not? How well do you they think the students understood the mathematics content in the physically active lessons? Can you give me a specific example? Do you think the PA aspect of the lesson contributed to greater engagement in the lesson compared to how that same mathematics content would usually be taught?

### Statistical methods

Statistical analysis of both the primary and secondary outcomes will be conducted with linear mixed models using SPSS statistics version 20 and alpha levels will be set at *p* > 0.05.

The models will be used to assess the impact of treatment (EASY Minds or control), time (baseline and post-test) and the group-by-time interaction, these three terms forming the base model. The models will be specified to adjust for the clustered nature of the data and will include all randomized participants in the analysis. Mixed models are robust to the biases of missing data and provide appropriate balance of Type 1 and Type 2 errors [43]. Mixed model analyses are consistent with the intention-to-treat principle, assuming the data are missing at random [44]. Sex and weight status (based on body mass index) will be included as covariates in the models. Further sub group analysis will be conducted based on sex, weight status, mathematical ability, and enjoyment of mathematics and on-task behaviour.

The focus groups and interviews will be digitally recorded with the participants’ consent and transcribed verbatim. A computer program (NVIVO 10) will be used to assist with the organisational aspects of data analysis. Analysis will be conducted by an independent qualitative researcher. Analysis will be performed using a standard general inductive approach to qualitative analysis. Initially, inductively derived codes or labels will, be formulated from the meaning units arising from the data. The developing coding scheme will be continually revised and further expanded after coding of additional transcripts. Following coding of all the transcripts, emerging themes will be identified and defined.

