**Flow of participants through the EASY Minds study**

### Sample size calculation

Power calculations were conducted to determine the sample size required to detect changes in the in the primary outcome of accelerometer-determined physical activity counts per minute (CPM) [27]. Calculations assumed baseline-posttest correlation scores of *r* = 0.30 and were based on 80% power, with alpha levels set at *p* < 0.05. Using the standard deviation (SD) of change observed in the EASY Minds pilot study (SD =200 CPM) and a conservative intra-class correlation coefficient (ICC = 0.15), it was calculated that a study sample of N = 200, with 8 clusters (i.e., schools) of 25 students would provide adequate power to detect a between group difference of 200 CPM across the school day.

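### The analysis section prints the significance threshold with the inequality reversed (p > 0.05), contradicting the p < 0.05 used for the sample size

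*Protocol article*

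**What the plan says.** The protocol article mentions a significance level in two places.

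- **Statistical methods.** The opening sentence covers the analysis of both primary and secondary outcomes by linear mixed models. It ends: "alpha levels will be set at *p* > 0.05".
- **Sample size calculation.** The power calculations "were based on 80% power", "with alpha levels set at *p* < 0.05". They lead to "a study sample of N = 200, with 8 clusters (i.e., schools) of 25 students", which is said to give adequate power to "detect a between group difference of 200 CPM across the school day".

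No other section gives a threshold or comments on the difference.

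**The concern.** The number is the same in the two sections and the inequality is opposite. The Sample size calculation section governs only the power calculation. The sentence in Statistical methods is the one a reader would consult for the prespecified criterion by which outcomes will be judged, and that is the sentence with the wrong sign.

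Read as a rule, it inverts significance: weak evidence would count as an effect and strong evidence would not. A published protocol is the public record of what was fixed in advance, so its decision threshold should not leave the reader to choose between two opposite signs.

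**Working it through.** **Step 1. Set the statements side by side.** Sample size: p < 0.05. Analysis of primary and secondary outcomes: p > 0.05. The level agrees and the direction does not.

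**Step 2. Ask which sign the article's own figures support.** Inputs, all from Sample size calculation unless noted:

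- difference 200 CPM and power 80%
- SD of change 200 CPM, from the pilot
- baseline to post-test correlation 0.30
- ICC 0.15
- 8 schools of 25 students, four schools per arm (Abstract, Methods/Design), so 100 students per arm

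Two-sided testing and a normal approximation are my assumptions.

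Design effect = 1 + (25 − 1) × 0.15 = 4.6.

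Total N = 2 × n per arm, where n = 2 × [SD × (1.960 + 0.842) / 200]² × 4.6, rounded up.

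Power at 100 per arm = Φ(200/SE − 1.960), where SE = SD × √(2 × 4.6 / 100) = SD × 0.3033.

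The text gives both an SD of change and a correlation, so the SD can be read in three ways:

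- **200 is the SD at one time point.** SD of change = 200 × √(2 × 0.70) = 236.6. Then n = 21.98 × 4.6 = 101.1, so 102 per arm and N = 204. SE = 71.8, and power at N = 200 is Φ(2.787 − 1.960) = 79.6%.
- **200 is the SD of change, as written.** n = 15.70 × 4.6 = 72.2, so 73 per arm and N = 146. SE = 60.7, and power at N = 200 is Φ(3.297 − 1.960) = 90.9%.
- **Baseline-adjusted SD.** 200 × √(1 − 0.30²) = 190.8, giving N = 132 and power 93.3% at N = 200.

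The first reading reproduces the stated 200 to within 2% (204 against 200) and the stated 80% power almost exactly. Under the other two, 200 students is more than enough. If one further assumes a t test on 6 cluster-level degrees of freedom, which the article does not state, power in the order listed is 64.4%, 78.4% and 82.0%.

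**Step 3. Apply the printed analysis rule literally.** Suppose p > 0.05 counts as significant.

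- With no true effect: probability of declaring one = 1 − 0.05 = 0.95.
- With a true difference of 200 CPM: probability of declaring it = 1 − power. Under the normal approximation this is 1 − 0.796 = 0.20, 1 − 0.909 = 0.09 or 1 − 0.933 = 0.07 in the three readings.

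None of these is near the stated 80%. The power statement is therefore compatible with p < 0.05 and not with p > 0.05.

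**Step 4. Effect of correcting the sign.** The sample size already rests on p < 0.05, so no figure in that section changes.

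**The case against.** The strongest reply is that nobody could be misled. One character is wrong, the level is the same in both sections, and the same Statistical methods paragraph defends mixed models for the way they balance the two types of error, which makes no sense with an inverted criterion. Both sections also express alpha, a number, as an inequality, so the readable content of each is simply 0.05. Nor does the article say in so many words that results above 0.05 will be declared significant. All of this stands, and it settles how serious the point is. It does not remove the contradiction, which lies in the decision threshold rather than in background text.

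A reader might infer more than the article supports:

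- **That the trial would run with a 95% false-positive rate.** That figure is only the literal consequence of the printed sign. Nothing suggests the team would analyse this way.
- **That leaving out one-sided or two-sided is a further defect.** A condensed article commonly leaves this to the full protocol or analysis plan. It is not stated wrongly here, and it has no bearing on the reversed sign.
- **That the sample size is compromised.** It was set with the conventional sign. How the SD of 200 CPM should be read is a separate matter.
- **That the threshold should be confined to one primary outcome.** The sentence covers primary and secondary outcomes, and this error gives no reason to narrow it.

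**Conclusion.** The point holds as an internal contradiction in the stated significance criterion, very likely a typographical error. It should be corrected because no other threshold is stated for the analysis. Its practical size is small: no design feature, model, outcome or sample size depends on the wrong sign.

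That the sign in Sample size calculation is the intended one rests on the shared level of 0.05 and on the power statement, which the reversed rule cannot satisfy under any of the three SD readings. The power figures assume two-sided testing and a normal approximation. The contradiction itself needs no assumption.

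**What to change.** In Statistical methods, replace the clause with a statement that the significance level is alpha = 0.05 and that results are called significant when p < 0.05, for both primary and secondary outcomes. This agrees with Sample size calculation, which needs no change.

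The cost is a one-line correction. The sample size, design and planned models stay as they are.
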